#### **Language learning arm:**

The intervention in the language (English) learning arm will be performed by teachers from the Carré International, a department from Caen University specialized in foreign language teaching and experienced in teaching to seniors. This intervention will consist in English exercises designed to reinforce each participant's abilities in understanding, writing and speaking.

#### **No intervention arm:**

No intervention will be delivered to participants assigned to this arm, during the study duration.

### 1.5 Randomization

The randomization list will be generated centrally by the biostatistician at the EUCLID clinical trials platform prior to the start of the study and kept confidentially in a secure environment. The sample size of each randomized group will be balanced with a ratio of about 1:1:1.

- Group 1: Meditation
- Group 2: Learning of English (active control)
- Group 3: No intervention

A working sheet presenting the entire randomization process will be kept confidentially at the EUCLID clinical trials platform

### 1.6 Eligibility criteria

#### 1.6.1 Inclusion criteria

##### For all participants

- Age  $\geq 65$  years;
- To be autonomous (assessed with the following question asked by the clinician: "would you be able to live alone (from a functional (not affective) point of view »?);
- Live in their home;
- Educational level  $\geq 7$  years (from the Preparatory Course (First grade) included);
- To be registered to the social security system;
- To be motivated to effectively participate in the project and to sign the consent form in agreement with the local ethic committee (Comité de Protection des Personnes);
- Neuropsychological performances within the normal range (according to age, sex, and educational level), as assessed by the diagnostic battery.

##### For participants without previous meditation practice

- French mother tongue;
- Available for the trial duration (24 months);
- Retired since 1 year or more;
- No preference regarding the intervention group;
- Not having regularly or intensively practiced meditation or comparable practices (yoga, Qi Gong, Alexander technique)
  - more than one day per week for more than six months consecutively over the last 10 years,
  - intensively (internship or retreat > five consecutive days) over the past 10 years,
  - more than 25 days of retreats (cumulatively) prior to the last 10 years;
- Not speaking English fluently.

##### For expert meditators

- Formal meditation practice > 10 000 hours in the whole life, including at least 6 cumulated months of retreat;
- Daily meditation practice (at least 6 days/week, 45 minutes/day);
- Mindfulness meditation practice (i.e. mindfulness, Samatha/ Vipassana, Zazen (Zen), Shikantaza (Zen), focused attention, Mahamudra/ Dzogchen), and compassion mediation practice (i.e. tonglen, metta / karuna, meditation on Bodhichitta).

#### 1.6.2 Exclusion criteria

- Contraindication to MRI or PET Amyvid® or PET Glucotep® ;
- For security reasons related with the use of Amyvid®, a blood sampling allowing to measure hepatic and renal functions will be performed at the V1 visit before the PET-Amyvid® scan. In case anomalies are detected of grade 3 or higher severity, the PET-Amyvid® scan will not be performed.
- Hypersensitivity to Amyvid® or Glucotep®
- Presence of a major neurological or psychiatric disorder (including an addiction to alcohol or drugs);

## STATISTICAL ANALYSIS PLAN

- History of cerebral disease (vascular, degenerative, physical malformation, tumor, or head trauma with loss of consciousness for more than an hour);
  - Presence of a chronic disease or acute unstable illness (respiratory, cardiovascular, digestive, renal, metabolic, hematologic, endocrine or infectious);
  - Current or recent medication that may interfere with cognitive action or radiological measures (psychotropic drugs, antihistamines, anti-Parkinsonian drugs, benzodiazepines, non-steroidal anti-inflammatory agents, antiepileptics, central analgesic and muscle relaxants);
  - Under legal guardianship or incapacitation;
  - Inclusion in another biomedical research protocol at baseline, if including use of a radiolabel for radiological measures;
  - Physical or behavioral inabilities to perform the follow-up visits as planned in the study protocol.
- Sample size

### **For the randomized clinical trial with non-expert seniors:**

The comparison of the meditation vs. no intervention arms will focus on the change in 1) volume and 2) metabolism of the anterior cingulate cortex from baseline to the end of the 18-months intervention, with an expected effect size of 0.75.

We expect the same effect size of 0.75 for the comparison between the meditation arm and learning of English arm on the change in 1) volume and 2) metabolism of the insula from baseline to the end of the 18-months intervention.

To demonstrate an effect size of 0.75 for each of the four comparisons, with 80% power and a two-sided type I error of 1.25% (Bonferroni correction for test multiplicity), 42 participants per arm need to be included for a total of 126 participants.

### **Experienced meditators :**

For recruitment capacity reasons, it is possible to recruit 30 experienced meditators in the study. With the inclusion of 30 experienced meditators and 126 non-expert seniors, our power to highlight an effect size of 0.74 in the comparison of brain imaging data with a significance level of 5%, is 95%.

## 1.7 Outcomes

### 1.7.1 Primary outcomes

For the comparison between meditation intervention and no intervention (**OBJECTIVE 1**):

- Change in anterior cingulate cortex volume (T1-weighted MRI) from baseline to 18 months;
- Change in anterior cingulate cortex perfusion (early PET-Amyvid® scan) from baseline to 18 months).

For the comparison between meditation intervention and language learning intervention (**OBJECTIVE 1BIS**):

- Change in insula volume (T1-weighted MRI) from baseline to 18 months;
- Change in insula perfusion (early PET-Amyvid® scan) from baseline to 18 months).

### 1.7.2 Secondary outcomes

#### **Behavioral outcomes (OBJECTIVES 2, 4, 6 et 7) :**

One composite score per cognitive area assessed by the neuropsychological tests and the questionnaires. The composite scores will correspond to the mean of z-scores calculated from all the cognitive scores obtained for the corresponding cognitive function that will have a normal distribution and will not have floor or ceiling effect. (Additional exploratory analyses will be conducted on all individual behavioural measures obtained).

#### **Radiological outcomes (OBJECTIVES 2, 4, 6 et 7):**

- Grey and white matter volume in all brain voxels;
- hippocampal and hippocampal subfield volumes;
- Brain perfusion in all brain voxels;
- Fractional anisotropy and mean diffusivity in all brain voxels;
- number, size, type and location of white matter lesions;
- magnetic susceptibility index in all brain voxels;

## STATISTICAL ANALYSIS PLAN

- brain functional connectivity measures in all brain voxels at rest in a non-meditative state ;
- Brain amyloid load (of the PET-Amyvid® radiotracer) measured in all brain voxels as well as in a global grey matter mask;
- Brain glucose uptake at rest;
- Brain activity measured with fMRI specifically associated with emotional processes (comparing emotional to neutral items) during the Rest-SoVT task.
- Brain activity measured with fMRI specifically associated with attentional processes (alertness, inhibition, sustained attention) during the AX-CPT task.

### Sleep-related outcomes (OBJECTIVES 2, 4, 6 et 7):

- Subjective measures of sleep collected via sleep questionnaires
- Data collected by actimetrics record (mean duration of sleep, fragmentation indices during activity and resting states, regularity of the rest-activity cycle).
- Data collected during polysomnographic sleep record: Total sleep time, Sleep onset latency, Sleep efficiency, % of Stage N1, % of Stage N2, % of Stage N3, % of Stage REM sleep, Wake After Sleep Onset (WASO), Apnea-hypopnea index (TST), Arousal index
- Data collected through Somno-Art.

### Biological outcomes (OBJECTIVES 2, 4, 6 et 7):

- Total cholesterol, Triglycerides, HDL-cholesterol, LDL-cholesterol, serum urea, serum creatinine, gamma glutamyl transferase, glutamate-oxaloacetate transaminase and glutamate-pyruvate transaminase, complete blood count, high-sensitivity CRP, Cytokines, insulin-like growth factor-1, Super Oxide Dismutase, Brain Natriuretic Protein, Estradiol, Dehydroepiandrosterone-Sulfate, Cortisol, Sex Hormone Binding Globulin, bioavailable testosterone, Thyroid Stimulating Hormone, serotonin, tissue plasminogen activator, PAI 1, Brain-Derived Neurotrophic Factor, Tau and PhosphoTau, Aβ 42, lymphocytic immunotyping, mRNA Lymphocytes, telomeres and telomerase, ApoE4, cDNA/mRNA REST, GWAS, circulating antibodies.

### Impact on participants' partners (OBJECTIVE 3):

- Questionnaires results

### Neural signature of meditation practices (OBJECTIVE 5) :

- Measure of neural activity in all brain voxels measured with resting-state fMRI as well as with fMRI during the SOVT-Rest task, in a mindfulness state versus a non-meditative state.  
Measure of neural activity in all brain voxels measured with resting-state fMRI as well as with fMRI during the SOVT-Rest task, in a compassion state versus a non-meditative state.

### Safety and acceptance (OBJECTIVE 2):

- Adverse events, measures of anxiety, depression, satisfaction, and well-being.

## 2. Statistical aspects

The statistical analysis of the primary outcomes (objectives 1 + 1bis) will be conducted by the biostatistician of EUCLID.

The statistical analysis of secondary outcomes will be performed by respective WPs dedicated to the evaluation of the different objectives as follows:

WP1 Meditation: [name]

WP2 Lifestyle: [name]

WP3 Attention: [name]

WP4 Emotion: [name]

WP5 Cognition and Wellbeing: [name]

WP6 Biomarkers: [name]

Details of the statistical aspects regarding those secondary objectives are listed in the corresponding Statistical Analysis Plan.

### 2.1 Analysis strategy

#### 2.1.1 Definition of analysis populations

Only participants presenting at least one of the following conditions can be excluded from the analysis:

- participants who never followed the study strategy (if they had no knowledge of the group they were randomized in);
- participants wrongly included with an unsigned consent;
- participants wrongly included for major non respected eligibility criteria;
- participants who withdrew their informed consent.

Decisions about exclusion will be made by the Trial Scientific Committee after documentation of observations by the EUCLID platform, blinded to the strategy group and to the participants' evolution after enrolment.

Except for these exclusions, the participants who died or who were lost to follow-up, or who interrupted the intervention or who left the study will all be included in the analysis.

Intent to treat analysis: All randomized participant will be included in the analysis in the group to which they were initially randomized and all their data is used, regardless of protocol deviations during the trial.

Per protocol analysis: randomized participants who attended at least 20% of their allocated interventions classes, or neither meditation nor foreign language classes if in the passive control group, and with primary endpoints available.

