### ***6.14. Premature termination of the trial***

In the event of premature discontinuation of the trial (withdrawal or withdrawal of consent), participants will receive standard clinical follow-up by their regular physician.

A participant is considered lost to follow-up when they stop the protocol follow-up without a reason known to the investigator, so that data collection cannot be conducted as planned. Participants lost to follow-up should be actively sought by the investigator.

A participant who wishes to withdraw their consent to participate in the research (as they is entitled to do at any time), is no longer followed within the framework of the protocol, but must receive the best possible care given their state of health and the state of knowledge at the time.

A withdrawal of consent is a decision, by an included participant to exercise their right to discontinue participation in a research study at any time during the course of follow-up, without incurring any prejudice as a result, and without having to provide a reason.

The investigator should identify the cause of the withdrawal of consent and assess whether it is possible to collect, for the participants included in the randomized clinical trial, the primary outcome variable at the time of withdrawal of consent.

Withdrawals of consent should be promptly notified to the sponsor. The reasons for and date of withdrawal of consent should be documented in the participant's case report and medical record.

No data will be collected after withdrawal of consent but previously collected data will be retained unless the participant objects in writing.

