### **11.3.3. Participants included in the analysis**

Only participants who meet at least one of the following conditions may be excluded from the analysis:

- Participants who never followed the research procedure (provided they were not aware of the group to which they were randomized),
- Participants wrongly included for unsigned consent,
- Participants who withdrew their consent.

This exclusion decision will be taken by the Scientific Council of the trial after documentation of the observation by the Methodology and Data Management Center (EUCLID), without regard to the strategy group and the participant's evolution after inclusion.

Apart from these exclusions, all participants who died, were lost to follow-up, or dropped out of the research will be included in the analysis.

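### The intent-to-treat set may drop randomised participants who withdraw consent, against the plan's own definition of that set and at odds with its data-retention rule

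*Combined protocol and SAP*

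**What the plan says.** Primary SAP 2.1.1 defines intent to treat in these terms: "All randomized participant will be included in the analysis in the group to which they were initially randomized and all their data is used". Protocol 11.3.1 gives the same definition for the main analysis.

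The same SAP section opens with a list of exceptions: "Only participants presenting at least one of the following conditions can be excluded from the analysis". One of the four conditions is "participants who withdrew their informed consent". Protocol 11.3.3 has the matching entry, "Participants who withdrew their consent", and the secondary SAP (Definition of analysis populations) repeats it. The primary and secondary SAPs also list "participants wrongly included for major non respected eligibility criteria", which protocol 11.3.3 does not.

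Both SAPs keep in the analysis those who died, were lost, stopped the intervention or left. Under protocol 11.3.1 and primary SAP 3.6.1, a missing primary outcome is replaced by the smallest change observed across all groups.

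Protocol 6.14 covers withdrawal itself. Nothing is collected afterwards, but "previously collected data will be retained unless the participant objects in writing". The investigator is also to "assess whether it is possible to collect, for the participants included in the randomized clinical trial, the primary outcome variable at the time of withdrawal".

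Exclusions are decided by the scientific committee, blinded to arm and to what happened to the participant after enrolment.

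**The concern.** An analysis that may remove people for something they did after randomisation is not an all-randomised analysis, whatever it is called. The risk is real here because participants are told their arm by telephone and mail (protocol 6.7). The same section arranges the announcement so as to limit dropout among people disappointed with their group, and section 11.2 calls for close monitoring of refusals once the group is known. So the protocol itself accepts that leaving may depend on allocation.

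The first exclusion in protocol 11.3.3 and primary SAP 2.1.1 recognises this. It removes people who never followed the procedure only if they did not know their group. The withdrawal entry has no such condition and no time limit, so even a participant whose 18-month scans are complete could be removed.

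The plan also treats similar dropouts in opposite ways. A person who withdrew consent may be deleted, while a person who was lost or left is kept and, with no 18-month value, scored at the worst change seen.

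**Working it through.** **1. The texts side by side.**
- Definition (protocol 11.3.1, primary SAP 2.1.1): every randomised participant, with all their data.
- Exception (protocol 11.3.3, both SAPs): withdrawers may be taken out.
- Retention (protocol 6.14): withdrawers' earlier data stay unless they object in writing, and the primary outcome is sought at withdrawal.

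The first two cannot both describe the primary set. The third means that, without a written objection, usable data would be on file for someone whom the second allows to be dropped.

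**2. The plan's own figure.** Inputs from the sample-size text: effect size 0.75, two-sided alpha 1.25%, power 80%, 42 per arm. The normal approximation, n = 2(z for alpha/2 + z for power)² / 0.75², gives 40 per arm. The noncentral t gives power of 79.7% at 41 and 80.9% at 42. The stated 42 is reproduced, and this point does not change it.

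**3. What exclusion does to the estimate.** Let w be the share of an arm that withdraws and d the mean change of those who stay minus the mean change of those who withdraw, in SD units. The mean of an arm without its withdrawers exceeds the all-randomised mean by w × d. The bias in the difference between arms is therefore (w × d in meditation) minus (w × d in the comparator). With 4 of 42 withdrawing in one arm only, w = 4/42 = 0.095, so each full SD of d moves the estimate by 0.095 SD. The documents give neither w nor d for any arm.

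**4. How far the two treatments differ.** Simulation: 10,000 runs, 42 per arm, SD 1, true difference 0.75, t test at 1.25%, dropout unrelated to outcome. The imputed value is the minimum over the three arms. The dropout counts are assumptions.

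| Dropouts, meditation / control | Excluded: estimate, power | Minimum imputed: estimate, power |
|---|---|---|
| 2 / 0 | 0.75, 80% | 0.60, 47% |
| 4 / 0 | 0.75, 79% | 0.45, 16% |
| 0 / 4 | 0.75, 77% | 0.98, 95% |
| 4 / 4 | 0.75, 76% | 0.68, 44% |

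With no true effect and 4 dropouts in one arm, rejection at the nominal 1.25% is about 1.4% under exclusion and 4.3% to 4.8% under imputation.

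**5. Reading the table.** Dropout here is unrelated to outcome (d = 0), so exclusion is unbiased by construction and the whole shift is produced by the imputed minimum. The table shows that the two treatments can give very different answers for the same people. It does not measure bias from exclusion, and it does not show that imputing the minimum is right.

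**The case against.** **The rule is permissive, explicit and blinded.** It says who can be excluded, not who must be. The decision is blinded to arm and to later course, and primary SAP 3.3 reports exclusions with reasons. This stands as protection against deliberate selection. It does not undo withdrawal that itself depends on arm, and no criterion says which withdrawers stay. Withdrawal is also itself an event after enrolment, so the committee cannot be blind to it.

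**Section 6.14 governs retention, not analysis.** This is correct: it asks only whether the outcome can be obtained and does not say that retained data enter the primary analysis. The firm contradiction is with the intent-to-treat definition; section 6.14 adds that removal is not needed unless the person objects in writing.

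**Withdrawal is not the only way out.** A participant unhappy with the allocation can stop the intervention and remain in follow-up (6.15.1). Entry requires no strong preference (4.2.1), and willingness is reconfirmed before randomisation (6.7). This makes arm-related withdrawal less likely but does not exclude it.

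**The labels are mostly defined.** A reader might infer that the site can move the primary result by its choice of label. Section 6.14 defines withdrawal as the participant's own decision, to be documented with date and reasons, and defines loss to follow-up separately. Only leaving the study lacks a definition, so that inference goes further than the text.

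**The eligibility entry matters less.** Entry criteria are verified before randomisation (6.6, 6.7), and wrongly included participants already go to the Scientific Council (6.15.3). What remains is that the lists differ and that the word major is undefined.

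**Conclusion.** The point holds as a matter of text. All three lists permit a post-randomisation exclusion that the intent-to-treat definition does not allow, so the primary set is a modified one under the wrong name. The maximum-bias analysis in primary SAP 3.6.1 replaces missing values; nothing says that it brings excluded withdrawers back.

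The size in this trial cannot be stated. No withdrawal rate is given, and protocol 11.2 only expects dropout after allocation is known to be very low. A reader might take the drop from 0.75 to 0.45 as the bias caused by excluding withdrawers. It is not: that shift comes from the missing = failure rule, assumes four dropouts in one arm and none in the other, and falls to 0.75 against 0.68 when both arms lose four.

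The change should be made: it is cheap and settles in advance who belongs to the primary comparison. Confidence is high on the conflict in wording; no claim is made about the direction or amount of bias.

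**What to change.** In protocol 11.3.3, primary SAP 2.1.1 and the secondary SAP:
- Restrict the withdrawal exclusion to participants who object in writing to use of their data, and report their number by arm.
- Analyse all other randomised participants in their allocated group with data collected up to withdrawal, including any 18-month scan already done. State how a scan obtained early, at withdrawal, is used, because the SAP defines the change at 18 months.
- Apply to withdrawers the same missing-data method and the same maximum-bias sensitivity analysis as to other dropouts.
- Align the major-eligibility entry in the two SAPs with the protocol list, or limit it to named criteria assessed before randomisation.

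Settle the missing = failure rule at the same time. If it is left as it stands, withdrawers without an 18-month value move from possible deletion to the minimum observed change, with the consequences shown in the table.

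Cost: up to five bullets in three documents (withdrawal in three lists, eligibility in two), one of them the protocol, plus a decision on the common missing-data method. No new data are needed.

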#### 2.1.2 Definition of strategies with missing data

Data available: inclusion of only participants whose data considered is available

Missing=failure: Any missing value will be replaced by the value corresponding to failure

Maximum bias strategy: Strategy comparing the results of two analyzes, one replacing missing data by a failure of the strategy in one group and by a success of the strategy in the other. And inversely in a second time.

#### 2.1.3 Type I error rate

The statistical tests for the main objectives (1 + 1bis) will be performed with 1.25% error rate each, controlling the family-wise error rate to 5% for the 4 comparisons.

### 2.2 Descriptive analysis

The frequency and proportion of available data will be described for each variable.

Qualitative variables will be described in terms of number, proportion and exact binomial confidence interval of proportion.

Quantitative variables will be described in terms of absolute frequency, mean, standard deviation, confidence interval of the mean, median, interquartile range, minimum, and maximum. Descriptive analysis will be performed overall and by intervention group.

